### 3.11 Definition of End of Trial

The end of trial is the date of the last data capture.

## 4 Process analysis

### 4.1 Qualitative work with Cohort 1 study participants

We are aiming to recruit up to 30 patients with type 2 diabetes from the intervention group only. The trial participant information leaflet will include information about the nature of the qualitative study and what it will involve for the participant if they decide to take part.

Participants in the interview study will be informed that their participation is entirely voluntary and if they do not wish to take part this will not affect their involvement in the feasibility trial or their care in any way.

Participants who have given consent will be interviewed twice. At the initial interview, participants will be asked questions including, sharing their experience of managing their diabetes medications, challenges with managing their condition etc. At the final interview, participants will be asked to share their views on the system and help the investigators understand how the messages were perceived, how they influenced adherence and self-management in general and identify issues around potential attrition and inform the final design of the main trial.

We will use purposeful sampling to recruit a diverse group of participants in terms of age, gender, duration of diabetes, ethnicity, socioeconomic status, comorbidity, medication use, illness experiences and familiarity with technology.

Interviews will be conducted over the phone at the beginning and the end of the 26-week follow up period ( $\pm$  4 weeks). They will be audio recorded and transcribed verbatim (the transcripts will be anonymised and will be kept in a secure location to protect the participants' anonymity and confidentiality).

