### 3 TRIAL DESIGN

#### 3.1 Intervention study

This is a primary care based, multicentre, 2-year (including a 26-week intervention), two-arm individually (1:1 ratio) randomised controlled, parallel group feasibility trial.

Patients with type 2 diabetes will be randomised to current care with individually tailored mobile device-based intervention encouraging and supporting them in developing a habit of taking their medication as intended and providing hints and tips to help them with other aspects of living with the condition (treatment arm) or to current care with the addition of infrequent non-health related messages (usual care arm).

The trial team will be blinded as to participant allocation to either the intervention or control arm. Investigators conducting qualitative interviews and focus groups with patients in the intervention arm will not be blinded to participant arm allocation but systems will be implemented to avoid clinicians or the trial team becoming aware of allocation status for individual participants. [See *Appendix A for study flowchart*].

Participants will receive messages for 26 weeks (approximately six months) from randomisation to final follow-up and remain in the trial for a further 18 months with data collected from their medical record. After the initial screening and eligibility check, informed consent will be obtained.

All participants will be followed-up at the end of the follow-up period post randomisation to collect questionnaire information (same as for baseline) and follow-up measures (same data collected for baseline). [See *Appendix B for a detailed schedule of procedures*].

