### **3.8.2 Follow-up (data collection)**

Follow-up will last for 26 weeks after randomisation. For ease of reference, all patient facing documentation will refer to this period as 'six months'. To address any issues that may arise (e.g. the participant is not able to receive messages), an unscheduled contact may be made during the 26 week follow up period if required.

Participants will be asked to complete the following questionnaires at 26 weeks ( $\pm$  4 weeks) following randomisation:

- MARS self-report scale
- EQ-5D-5L
- A measure based on health psychology theory and the technology acceptance model.
- Healthcare utilisation record

The 26-week follow-up questionnaires will be posted to the participant or a link will be given to them via email. If the participant's follow-up questionnaires have not been received one week after the due date, the trial team will contact the participant to remind them to complete these online or on paper. Multiple attempts will be made within the determined window ( $= \pm$  4 weeks).

If participants choose to complete the 26-week measures online, they will be required to log in to the electronic questionnaires using the same electronic verification process used at baseline assessment.

Follow up data will be obtained from the medical record and provided to the trial team for the period of 26 weeks after recruitment: HbA1c, systolic and diastolic blood pressure, total and HDL cholesterol, weight, height, current medication and prescriptions for diabetes drugs (glucose lowering, blood pressure lowering and lipid lowering). Data collection will be through one of the following routes: provision of a medical summary provided by the GP practice team or a 26-week notes review CRF completed by a nurse or facilitator or a trial team member visiting the surgery.

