## 6 STATISTICS

### 6.1 Description of Statistical Methods

The analysis will be carried out once the final patient has completed their 26-week follow up. An intention to treat approach will be used, where all participants randomised will be included in the group to which they were allocated, regardless of intervention received. The results of the primary and secondary objectives will be presented descriptively using proportions and 95% confidence intervals.

The primary outcome will be the number of patients recruited and randomised as a proportion (with 95% confidence interval) of the target recruitment number.

Secondary outcomes, including loss to follow up (%), withdrawals (%) and completeness of data collection for various outcomes (%), will be presented overall and separately by treatment group.

Exploratory outcomes (changes in primary and secondary measures to be used in the main trial) will be analysed using an intention to treat approach. Continuous outcomes will be analysed using an analysis of covariance adjusting for minimisation factors. Results will be presented as a difference in means with 95% confidence interval. Binary outcomes will be analysed in a similar way using log binomial regression models (adjusting for minimisation factors). Results will be presented as relative risks with 95% confidence intervals.

A detailed statistical analysis plan will be prepared prior to data lock.

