### 6.2 The Number of Cohort 1 Participants

With 200 participants (100 in each group) the feasibility trial is powered to detect 80% follow up within 95% confidence intervals of 73.8% to 85.3%.

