| Randomisation                                                                   |                                                                                                                             | x                                                                             |                                               |                      |                               |
| Text Messaging System Registration                                              |                                                                                                                             | x                                                                             |                                               |                      |                               |
| Intervention or Control procedures                                              |                                                                                                                             |                                                                                      | x                                      |                      |                               |
| Scheduled and Unscheduled Contacts                                              | x                                                                                                                    | x                                                                             | x                                      | x             |                               |
| 26-Week (± 4 weeks) Data collection                                             |                                                                                                                             |                                                                                      |                                               | x             |                               |
| Qualitative patient interviews for intervention group                           |                                                                                                                             |                                                                                      | x                                      | x             |                               |

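### Two telephone interviews given to up to 30 intervention participants and no controls, the last in the 26-week questionnaire window with no stated order, may raise questionnaire return and prime self-reported adherence in one arm

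*Protocol*

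**What the plan says.** Protocol section 4.1 sets up the qualitative work with trial participants: "We are aiming to recruit up to 30 patients with type 2 diabetes from the intervention group only". The schedule in Appendix B agrees, listing "Qualitative patient interviews for intervention group". On number and timing, 4.1 says "Participants who have given consent will be interviewed twice" and "Interviews will be conducted over the phone at the beginning and the end of the 26-week follow up period", with a tolerance of ±4 weeks. The first interview covers how the person manages diabetes medicines. The final one covers how the messages were received, how they affected adherence, and attrition.

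Section 3.8.2 collects MARS, EQ-5D-5L, the health psychology and technology acceptance measure, and healthcare use at 26 weeks, also ±4 weeks. Late returners in both arms are chased: "Multiple attempts will be made within the determined window".

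Section 3.1 describes a "two-arm individually (1:1 ratio) randomised controlled, parallel group feasibility trial", and section 6.2 assumes 100 per group. Under section 6.1, loss to follow-up, withdrawals and completeness "will be presented overall and separately by treatment group". Exploratory outcomes are compared between arms with adjustment for the minimisation factors.

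Section 3.1.1 mentions both qualitative interviews and debriefing calls after follow-up, and refers the reader to 4.1, which does not mention such calls.

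**The concern.** Research contact is unequal by arm. Beyond the reminders and unscheduled contacts open to everyone, up to 30% of the intervention arm has two conversations with researchers about medicines and adherence, and no control does. The topics overlap with what MARS and the mechanism questionnaire measure.

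There are two possible routes to bias. A final interview held before the questionnaire is returned may act as an extra reminder. It may also prime the answers about adherence and beliefs. In a by-arm table either effect would look like an effect of the messages.

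This bears on two uses of the data. Follow-up is the quantity that section 6.2 uses to justify the sample size, and it will inform planning of the main trial. Section 3.1.1 also makes absence of change in the mechanism measures one of the conditions for dropping a message type. If interviews moved those measures, that condition could fail and disliked content could be kept.

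**Working it through.** **Inputs from the protocol:** 200 participants, 100 per arm (6.2); up to 30 interviewees, all in the intervention arm (4.1, Appendix B); expected follow-up 80% with 95% CI 73.8% to 85.3% (6.2).

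**Assumptions, not in the protocol:** follow-up is 80% in everyone not interviewed; interviewees' follow-up r lies between 80% and 100%, so being interviewed does not lower it; all 30 places are filled unless stated.

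**1. The plan's own figure.** The exact (Clopper-Pearson) 95% interval for 160/200 is 73.8% to 85.3%, which matches 6.2. The half-width is 80 − 73.8 = 6.2 points below and 85.3 − 80 = 5.3 points above.

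**2. Share exposed.** 30/100 = 30% of the intervention arm, 0% of controls, and 30/200 = 15% of all randomised.

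**3. Follow-up.** Intervention arm = 0.30 × r + 0.70 × 0.80; control = 0.80; overall = the mean of the two.

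| Interviewee follow-up (assumed) | Intervention arm | Gap between arms | Overall | Overall shift |
|---|---|---|---|---|
| 80% | 80.0% | 0 | 80.0% | 0 |
| 85% | 81.5% | 1.5 | 80.75% | 0.75 |
| 90% | 83.0% | 3.0 | 81.5% | 1.5 |
| 95% | 84.5% | 4.5 | 82.25% | 2.25 |
| 100% | 86.0% | 6.0 | 83.0% | 3.0 |

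With 20 or 10 interviewees the largest gap is 0.20 × 20 = 4 points or 0.10 × 20 = 2 points.

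**4. Set against precision.** The 95% half-width of the between-arm difference at 80% and 100 per arm is 1.96 × √(2 × 0.8 × 0.2 / 100) = 11.1 points. The largest gap, 6 points, lies inside it. The largest overall shift, 3 points, is about half the 5.3 to 6.2 point half-width of the overall rate.

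**5. Self-reported adherence.** If being interviewed shifts MARS by d standard deviations, the arm mean shifts by 0.30 × d. For an assumed d of 0.1 to 0.5, that is 0.03 to 0.15 SD. If all 30 interviewees return and completers number 86, the share is 30/86 = 34.9% and the shift is 0.03 to 0.17 SD. The half-width of the difference in means with 80 completers per arm is 1.96 × √(2/80) = 0.31 SD.

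**6. Order of events.** The final interview and the questionnaires share one window, weeks 22 to 30, and one column of Appendix B. No passage fixes which comes first:
- Section 3.1.1 speaks of debriefing calls after follow-up, but does not tie them to questionnaire return or say whether they are the final interviews.
- Section 3.6 tells participants that their last contact is for the 26-week questionnaires, yet allows extra contacts for the qualitative work.

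The first interview precedes the 26-week questionnaires in any case, so ordering the final interview does not remove whatever effect the first may have.

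**The case against.** Interviewing only message recipients follows from the aim of learning what they thought of the messages, and is a reasonable choice. That stands, and the point is about timing rather than about who is interviewed.

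A reader might infer that the interviews do bias the results, by some 4 to 6 points in follow-up. The protocol does not support that. It gives no interview effect on return or on MARS. Those values arise only if every interviewee is retained and the interview is the reason. Interviewees are volunteers and may have stayed anyway, in which case the artefact is zero. Reminders, repeated attempts and the £10 voucher (10.6) already apply to both arms and may leave little for an interview to add.

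A reader might also extend the concern to all outcomes. Recruitment and randomisation are unaffected. HbA1c, blood pressure, cholesterol and prescribing data come from GP records, so a prompt to return a questionnaire does not change their completeness.

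A third inference would be to plan the main trial's attrition on the non-interviewed participants. That can do more harm than the problem it addresses. If true retention is 80 of 100 and all 30 volunteers would have stayed regardless, the other 70 show (80 − 30)/70 = 71.4%, which is 8.6 points too low.

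Finally, an analysis by interview status may be in the statistical analysis plan, which is not shown, so its absence from section 6.1 is not a fault. The order of interview and questionnaire is different: it is a rule of conduct that no analysis plan can restore once the data are collected.

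**Conclusion.** The point holds as a risk of unequal contact, not as a demonstrated bias. Up to 30% of one arm and none of the other has two interviews on topics that overlap the self-reported outcomes, and the final one may come before the questionnaire. On the stated assumptions the effect on follow-up is 0 to 6 points between arms and 0 to 3 points overall. The effect on MARS and the mechanism measures cannot be sized from the protocol, and the 0.03 to 0.17 SD shown above only illustrates assumed interview effects. Thirty is a ceiling that depends on consent, and fewer interviewees shrink these figures in proportion. What is exposed is questionnaire return and self-report. These results are secondary or exploratory, but they feed main-trial planning and the rule on omitting messages. The change is worth making because it is cheap and has to be made before the final interviews take place.

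**What to change.** - **Section 4.1:** state that the final interview takes place only after the participant's 26-week questionnaires have been returned or, for non-returners, after the questionnaire window has closed. Extend the interview window beyond the present ±4 weeks, since non-returners could not otherwise be interviewed within it.
- **Sections 3.1.1 and 4.1:** reconcile them, saying whether the debriefing calls after follow-up are the final interviews or a separate contact and, if separate, applying the same order.
- **Optional:** keep an interviewee flag with the qualitative team until data lock, because the flag reveals allocation. Then show questionnaire return and MARS by interview status as a description only. Do not use the non-interviewed figure alone to plan main-trial attrition, because interviewees are self-selected.

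The cost is that a few final interviews fall slightly later. Questionnaire-return status must also reach the unblinded interviewers by a one-way route, so that the trial team does not learn allocation (section 3.1).

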### 4.2 Focus Group Work with Cohort 2 Health Care Professionals

We are aiming to recruit a minimum of 12 and up to 30 staff at GP practices that are taking part in the trial to take part in focus groups or individual interviews. The final sample size will be determined by data saturation that is when no novel categories, themes or explanations are identified in additional interviews.

Each focus group will take place on one occasion. Additional face-to-face, telephone interviews or surveys will also be conducted if key staff are unavailable to attend planned focus groups.

Healthcare professionals will be informed that we will be recruiting for this qualitative study at the site initiation visit/study training. They may then be approached with information about the study, mainly via email or phone.

Healthcare professionals that express interest in taking part will be provided a participant information leaflet and consent form via email or post. The participant information leaflet will detail the nature of the study, what it will involve for the participant and any risks involved in taking part. Participation is entirely voluntary.

Where healthcare professionals are interviewed face-to-face a consent form will be provided and signed before the interview commences. Where interviews are carried out over the phone, consent will be audio recorded. The researcher will read each of the statements from the consent form and ask the participant if they agree; this will be audio recorded to document their informed consent.

The main purpose of this sub-study will be to identify the context of, and potential barriers and facilitators to implementation of the text-based system as a tool providing support for adherence to medications for patients with type 2 diabetes who have had a recent change in medication or were recently prescribed a new treatment. Specifically, we will explore staff experiences of recruiting for this study, how the intervention was implemented during the feasibility trial, and how the intervention could be implemented into routine clinical care.

Data collection will run throughout the trial period defined in this protocol.

Focus group discussions and interviews will be audio recorded and transcribed verbatim. The transcripts will be anonymised and kept in a secure location with access to authorised personnel only to protect participants' anonymity and confidentiality.

If a participant withdraws from the study, their data up to that point will be used in the analysis. Especially, for participants taking part in focus groups, it will not be made possible to isolate and remove individual comments from a group discussion.

## 5 SAFETY REPORTING

### 5.1 Definitions

An elective hospital admission will not be considered a serious adverse event.

|                       |                                                                                                                                                                                                                                                                                                                                                                                                                                                                                                                                                                                             |
|-----------------------|---------------------------------------------------------------------------------------------------------------------------------------------------------------------------------------------------------------------------------------------------------------------------------------------------------------------------------------------------------------------------------------------------------------------------------------------------------------------------------------------------------------------------------------------------------------------------------------------|
| Adverse Event (AE)    | Untoward medical occurrences which are not necessarily caused by or related to the intervention will not be collected as part of the feasibility trial.                                                                                                                                                                                                                                                                                                                                                                                                                                     |
| Adverse Reaction (AR) | 
An untoward and unintended response in a participant which is related to a participant using their mobile phone as part of this intervention.
 
"Response" means that a causal relationship between using a mobile phone as part of this intervention (i.e. to read messages) and an AE is at least a reasonable possibility, i.e. the relationship cannot be ruled out.
 
All cases judged by either the reporting medically qualified professional or the Sponsor as having a reasonable suspected causal relationship to the intervention qualify as adverse reactions.
 |

|                                                       |                                                                                                                                                                                                                                                                                                                                                                                                                                                                                                                                                                                                                                                                                                                                                                                                                                                                                                                                                                                                                                                                                                                                                                                                                                                                         |
|-------------------------------------------------------|-------------------------------------------------------------------------------------------------------------------------------------------------------------------------------------------------------------------------------------------------------------------------------------------------------------------------------------------------------------------------------------------------------------------------------------------------------------------------------------------------------------------------------------------------------------------------------------------------------------------------------------------------------------------------------------------------------------------------------------------------------------------------------------------------------------------------------------------------------------------------------------------------------------------------------------------------------------------------------------------------------------------------------------------------------------------------------------------------------------------------------------------------------------------------------------------------------------------------------------------------------------------------|
| Serious Adverse Event (SAE)                           | 
A serious adverse event is any untoward medical occurrence that:
 
 
• results in death
 
• is life-threatening
 
• requires inpatient hospitalisation or prolongation of existing hospitalisation
 
• results in persistent or significant disability/incapacity
 
• consists of a congenital anomaly or birth defect.
 
 
Other 'important medical events' may also be considered serious if they jeopardise the participant or require an intervention to prevent one of the above consequences.
 
N.B. The term "life-threatening" in the definition of "serious" refers to an event in which the participant was at risk of death at the time of the event; it does not refer to an event that hypothetically might have caused death if it were more severe.
 
N.B. In this trial, we will not be collecting SAEs for:
 
 
○ scheduled hospital visits
 
○ hospitalisation due to diabetes or any other underlying conditions
 
○ congenital anomalies or birth defects
 
○ any life-threatening medical occurrence that is not related to the intervention or participation in the trial
 
 |
| Serious Adverse Reaction (SAR)                        | 
An adverse event that is both serious and, in the opinion of the reporting Investigator, believed with reasonable probability to be due to one of the trial treatments, based on the information provided e.g. a car accident due to mobile phone use while driving resulting in inpatient hospitalisation.
                                                                                                                                                                                                                                                                                                                                                                                                                                                                                                                                                                                                                                                                                                                                                                                                                                                                                                                                                      |
| Suspected Unexpected Serious Adverse Reaction (SUSAR) | 
A serious adverse reaction, the nature and severity of which is not consistent with the information about the intervention in question.
                                                                                                                                                                                                                                                                                                                                                                                                                                                                                                                                                                                                                                                                                                                                                                                                                                                                                                                                                                                                                                                                                                                          |

Other 'important medical events' may also be considered serious if they jeopardise the participant or require an intervention to prevent one of the above consequences.

The term "life-threatening" in the definition of "serious" refers to an event in which the participant was at risk of death at the time of the event; it does not refer to an event which hypothetically might have caused death if it were more severe.

To avoid confusion or misunderstanding of the difference between the terms "serious" and "severe": "Severe" is often used to describe intensity of a specific event, which may be of relatively minor medical significance. "Seriousness" is the regulatory definition supplied above.

